### Informed consent

A written Informed Consent from the subject’s parents/caregiver is an inclusion criterion without which the subject cannot be included in the study.

### Randomisation, blinding, coding and data management

The participants will be randomized at recruitment to either the Nordic diet (ND, intervention) or the Regular (control) group (Fig. 1). Group affiliation will be blinded for participating families and the researchers. Boys and girls will be randomised separately in blocks of 10 from a pre-printed, computer-generated list available to the research nurses, who will enter in participants consecutively. Each participant will be given a unique study identification number. The identification number together with the date of birth will serve as identification on all forms, questionnaires, measurements and as participant identifier in the study database. The key identifying each individual with the unique identification number will be kept in a locked safe to which only researchers and administrative staff at Paediatrics, Department of Clinical Sciences has access. All data collected will be regarded as confidential and stored electronically in coded format according to the Swedish Personal Data Act (1998:204) and the European Union General Data Protection Regulation (EU 2016/679), but paper copies of forms will be kept as well.

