### Introduction of complementary feeding

The switch from the liquid diet of the young infant to the mixed diet of the older infant or toddler is a gradual process. First, when the infant starts showing interest in other foods the parent or caretaker offers small taste portions of various simple foods to take benefit of the infant’s curiosity. These small titbits, in Sweden usually served as purees or mashes of various vegetables, are provided as a way to familiarise the infant to new flavours and consistencies of foods which the infant will eat in the future, but they contribute little to the total energy and nutrient intake of the infant, which at this time is covered by breast milk or infant formula. Later, as the infant grows and develops many parents start substituting one or more breast- or formula-feeds with more and more solid food.

The ND group will be given recipes for fruit, berries and vegetable purees and instructions how to prepare these recipes at home. The main ingredients will be fruits, berries and vegetables which grow and are available in the Nordic region [26]. The dishes will be given as small taste meals to the participating infant when the parents feel it prudent to start offering the infant other foods besides breast milk or formula and the infant is deemed ready by the parent. This time-point is to be chosen by the parents themselves. When the time has come for taste meals, the instructions to the parents will be that they should systematically introduce eight different fruits, berries and vegetables, each one given at least 3 times daily for three consecutive days whether or not the child immediately appreciates the flavour/consistency the first time. After the first 3 days, the parent will switch to another fruit, berry or vegetable until the different ingredients have been sampled. In total, there will be a maximum of 72 exposures during 24 days.

The control group will be given the standard, oral and written advice that is given from well-baby clinics to parents when beginning with small taste meals based on national guidelines [52].

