#### The regular diet group

The regular diet group will function as control for to the ND group (Fig. 1). The participants will be given the current advice on infant feeding issued by the Swedish National Food Agency [52]. They will also be given regular, commercially available MCD, porridge, baby milk and BIG. No advice or recipes for meals will be given apart from the current recommendations.

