### Parental support

Parents with children in the ND group will be given support to continue following the dietary intervention. They will be invited to participate in a closed Facebook™ group. In this forum parents can discuss with a study dietician and among themselves, sharing experiences. Parents will also have instructional videos on the preparation of certain study foods available within the group setting. Participants in the group will share experiences and other information at their own discretion. No data will be collected through this group, but the group may function as a way to inform the families that participate in the group about upcoming study events and remind participants to send in questionnaires, etc.

Both the intervention and the control groups will get monthly telephone calls from a research nurse or a study dietician as part of the regular data collection (see below).

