#### Data on atopic disease and allergic manifestations

Family history of allergies, atopic diseases and asthma among parents and siblings will be collected at baseline. At 9, 12 and 18 mo. of age the participants will be asked for symptoms of allergy, asthma and atopic disease, and the research nurse will use a score sheet to assess eczema [69].

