### Procedures

The baseline and 9, 12 and 18 mo. visits will take place at the Paediatric Research Unit at the Department of Clinical Sciences, Paediatrics, Umeå University Hospital.

At baseline, the researchers will establish that the participant fulfils all the inclusion criteria and none of the exclusion criteria, written informed consent will be collected if this has not been collected earlier and the parents will be given spoken and written information about the study and time to ask questions on the study procedures. The parents will also be given information on how to complete questionnaires and forms, whether on-line or on paper, how to upload photos and, if the participants are randomized to the ND group, how to access the on-line support forum, i.e. the closed Facebook group of the study. The participants will then be assessed according to the Figure including drawing blood samples and provided with a month’s supply of study products and recipes.

At ages 7 and 8 mo., the research nurse or dietician will have a telephone follow-up with the participants checking adherence, possible study related problems, supply and consumption of study products and symptoms registrations.

At age 9 mo. the participants will again come to the Paediatric Research Unit for measurements according to the Figure.

At ages 10 and 11 mo. the research nurse or dietician will have a telephone follow-up with the participants checking adherence, possible study related problems, supply and consumption of study products and symptoms registrations.

At 12 mo. of age, the participants will again come to the Paediatric Research Unit for providing samples according to the Figure. Further, the research nurse will do a home visit for anthropometric measurements, administration of the deuterium labelled water and the two videotaped tests, i.e. food acceptance test and the attention free play test.

At ages 13–17 mo., the research nurse or dietician will have a telephone follow-up with the participants checking adherence, possible study related problems, supply and consumption of study products and the symptoms registrations.

Finally, at 18 mo. of age, the participants will come for the final measurements of the study according to the Figure. The research nurse will again do a home visit for anthropometric measurements, administration of the deuterium labelled water and the two videotaped tests, i.e. food acceptance test and the attention free play test.

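### The protocol says families and researchers are blinded, but its own procedures reveal the group to Nordic diet families, the research nurses and the study dietician

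*Protocol article*

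**What the plan says.** The section on randomisation, blinding, coding and data management states: "Group affiliation will be blinded for participating families and the researchers". The same section says that allocation is taken "from a pre-printed, computer-generated list available to the research nurses, who will enter in participants consecutively".

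Other sections describe what each arm receives:

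- **Introduction of complementary feeding:** "The ND group will be given recipes for fruit, berries and vegetable purees and instructions how to prepare these recipes at home". For controls: "The control group will be given the standard, oral and written advice that is given from well-baby clinics to parents".
- **The regular diet group:** "No advice or recipes for meals will be given apart from the current recommendations".
- Help promised to one arm alone, in the section on parental support: "Parents with children in the ND group will be given support to continue following the dietary intervention". This support is a closed Facebook group with a study dietician and instructional videos.
- **Procedures (baseline visit):** parents are told, "if the participants are randomized to the ND group, how to access the on-line support forum".
- **Data on atopic disease and allergic manifestations:** "the research nurse will use a score sheet to assess eczema".

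The power calculation section names fat mass from total body water as the primary outcome. Table 1 lists a wider primary set that includes anthropometry and blood pressure.

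**The concern.** A blinding statement tells readers how far to trust outcomes that depend on someone's report or judgement. Many outcomes here are of that kind: food records, eating behaviour, temperament, developmental milestones, symptoms and eczema. A parent who has been asked to work at a healthier diet may record meals or answer questionnaires differently from one who has not. A nurse who knows the group may score eczema or judge an adverse event differently. If the sentence stands, a reader could give these results the weight of masked assessment, which the design does not provide. Delivering a whole-diet intervention openly is not an error. The error is describing it as blinded.

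**Working it through.** No figure is at issue, so the check sets the blinding sentence against the procedures for each party, and then asks which outcomes each party produces.

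**1. ND families.** They are asked to introduce eight named fruits, berries and vegetables, each at least 3 times a day for 3 days. That gives 8 × 3 × 3 = 72 exposures over 8 × 3 = 24 days, which matches the totals in the article. They also receive main-meal recipes, with a recommendation to cook from them at least once daily, and an invitation to the forum. Controls are offered none of this, and no sham schedule, matching recipes or control forum is described. Even if the protein-reduced drinks and cereals could be masked, the rest of the package would reveal the group. The statement fails for these families.

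**2. Control families.** They receive commercial products, standard advice and the same monthly calls. Nothing they are given names their group. The Discussion, however, expects the focus on the Nordic diet to influence who enrols, which suggests that families know of that focus beforehand. A family that then receives no Nordic recipes can plausibly infer its group. What the recruitment material told them is not shown.

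**3. Research nurses.** They have access to the list and enter participants from it. The statement fails for them on list access alone.

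**4. Study dietician.** A dietician who takes part in an ND-only forum knows which parents there are ND parents. Monthly adherence calls to both arms are made by a nurse or a dietician, and they cover consumption of study products.

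**5. Laboratory analysts, video raters, statistician.** All forms and measurements carry a study number, so these roles could work without group labels. The article does not say that they do.

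**Outcomes by source:**

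- *Parent-reported:* five-day food records and the Children's Eating Behaviour Questionnaire; the Toddler Behaviour Questionnaire and the Ages and Stages Questionnaire; allergy symptoms; the symptom forms. All are exposed.
- *Parent-delivered:* the videotaped test meal. Its rating may be blind, but the parent serves the meal.
- *Nurse-assessed:* eczema score, adverse events and length. All are exposed. Length falls within the anthropometry that Table 1 lists as primary.
- *Fat mass by deuterium:* total body water comes from isotope analysis at an external laboratory. Fat mass is body weight less the fat-free mass derived from total body water. Weight is read on electronic scales in triplicate, and length does not enter. There is little room for observer influence.
- *Blood and faecal assays:* objective, and possible to run on coded samples.

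No section describes separate unblinded and blinded staff.

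**The case against.** The strongest reply accepts the inconsistency and disputes its weight. The sentence is the article's only blinding claim. The Abstract calls the study randomised and controlled, the Discussion does not list blinding among the strengths, and no outcome section calls an assessment blinded. The primary outcome is largely objective, as are most of the other primary outcomes. This stands, and it limits the severity.

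A reader might go further in several ways that the documents do not support:

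- *That all 250 families are unblinded.* The procedures establish this for the ND arm. For controls it is plausible but undocumented.
- *That essentially every secondary outcome outside the laboratory is compromised.* Rating of the two video tests involves an outside institution and may be blind.
- *That nurses run the ND support.* Only a study dietician is named in the forum. The nurses' knowledge comes from the list.
- *That results will be reported as blinded.* This is a risk that the sentence creates. It is not something the article shows.

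Two defences do not succeed. One is that only the products are meant to be masked, but the sentence refers to group affiliation. The other is that researchers means laboratory staff or analysts. The article does not say so, and that reading would leave the claim about families untouched. Nor is this an omission that a fuller protocol could cure, because a positive statement is contradicted by other sections of the same article.

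**Conclusion.** The blinding statement is wrong as written for ND families (planned as 125 of 250), for the research nurses and for the study dietician. Control families may also know their group. The consequence falls on parent-reported outcomes, the parent-served test meal, and nurse-assessed eczema, adverse events and length. Deuterium fat mass is little affected.

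The conclusion assumes that the procedures are carried out as described and that no masking exists beyond what the article reports. The size of any bias cannot be derived from the document, and none is claimed. No planned analysis changes; what changes is how certain results may be described and interpreted. Severity: should-fix.

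**What to change.** Replace the sentence with wording such as: *Families, research nurses and dieticians are not blinded to group. Laboratory analysts, video raters and the statistician work on coded data without group labels.* The second half should be printed only for the roles where it is true.

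Do not describe parent-reported or nurse-scored outcomes as blinded, and interpret them as open-label in reports.

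Where existing staffing allows, have the remaining 12- and 18-month anthropometry and eczema scoring done by a nurse who neither uses the allocation list nor makes the adherence calls. Recruitment ended in February 2018 with 250 included, so changing who holds the list cannot restore masking for enrolled families. Data collection runs to February 2019, so separating assessors can help only at visits still to come.

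The cost is a change of wording and, if feasible, a rota rule. The downside is that the trial can no longer be described as blinded for families and study staff.

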### Participants and recruitment

Through invitation-letters sent to all infants in Umeå municipality at 3 mo. of age, healthy, full-term singletons will be recruited. When parents consider it appropriate to introduce complementary foods into the diet of their child, but no later than at 6 mo. of age, the child will be randomly allocated to one of two study groups, i.e. the Nordic diet group (intervention, ND) or the Regular diet group (control).

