#### Exclusion criteria

Children with chronic illnesses that will affect feeding or growth, including food allergies or intolerance to study productsIntake of any complementary food at recruitmentUse of supplements or medications that will affect the study outcomesIron deficiency (Hb < 105 g/L, serum (S-) ferritin < 12 μg/L) or any other biochemical abnormality discovered at the baseline examination that needs medical attention after decision by the study physician.Repeated non-adherence to key study procedures including anthropometric measurements, allergy, eczema and symptoms registrations.

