### Trial status

Recruitment started April 2015 and ended February 2018 with 250 participants included. Data collection will continue until February 2019.

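### The allocation list is available to the nurses who enter infants and no masking is described, so concealment is not assured and selection at entry is possible

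*Protocol article*

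**What the plan says.** All places are in the protocol article.

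- **Randomisation, blinding, coding and data management.** The sequence is stratified by sex and uses a single stated block size of 10. On who has access to it: "computer-generated list available to the research nurses, who will enter in participants consecutively". On timing: "The participants will be randomized at recruitment to either the Nordic diet". On blinding: "Group affiliation will be blinded for participating families and the researchers". The nurses are not named in the blinding sentence. The locked safe in this section protects the key that links identity to study number, not the allocation list.
- **Participants and recruitment.** The moment of allocation depends on the family: "When parents consider it appropriate to introduce complementary foods into the diet of their child, but no later than at 6 mo. of age".
- **Exclusion criteria.** A biochemical abnormality found at baseline can exclude a child if it is one "that needs medical attention after decision by the study physician". Repeated non-adherence to key procedures is also listed as an exclusion.
- **Procedures.** "At baseline, the researchers will establish that the participant fulfils all the inclusion criteria and none of the exclusion criteria". At the same visit blood is drawn, and families in the Nordic diet arm learn how to reach the online support group.
- **Trial status.** "Recruitment started April 2015 and ended February 2018 with 250 participants included".

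**The concern.** Concealment means that whoever brings a child into the trial cannot know the next arm. Here the article gives the list to the staff who enter participants and mentions nothing that hides its contents. The blinding sentence does not settle this: it concerns families and researchers, and blinding after allocation is a different safeguard from concealment before it.

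Foreknowledge needs an opening to do harm, and the article leaves several. Entry time is elective within a window. One exclusion rests on judgement. Randomisation is placed at recruitment while eligibility is confirmed at the baseline visit, so as written an exclusion can follow allocation.

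At stake is the comparability of the arms. Neither intention-to-treat analysis nor a larger sample removes selection at entry. The primary outcome, fat mass, is measured only at 12 and 18 months (Body composition), so an imbalance in it at entry can be neither seen nor adjusted for directly. The Discussion counts individual randomisation as a strength of the study.

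**Working it through.** **1. The plan's own figure.** Inputs from Power calculation and statistical analyses: SD 0.6 kg, difference 0.24 kg, α = 0.05 (taken as two-sided), power 80%, attrition 20%.

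n per group = 2 × (1.96 + 0.84)² × (0.6/0.24)² ≈ 98.1, or 99 with rounding up. Then 99/0.8 = 123.75, or 124, against 125 stated. The sample size reproduces and is not in dispute.

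**2. How much of the sequence could be known.** Assume 5:5 within each block of 10 (the article implies 1:1 by its equal groups). With m = 5:

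| Situation | Next allocation called correctly | Certain in advance |
|---|---|---|
| List readable | 10 of 10 (100%) | 10 of 10 |
| List hidden; past allocations and block size known | m + (4^m / C(2m,m) − 1)/2 = 5 + (1024/252 − 1)/2 = 6.53 of 10 (65%) | 2m/(m+1) = 10/6 = 1.67 of 10 (17%) |
| List held elsewhere, blocks not trackable | about 50% | none |

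Access to the list dominates. The block size matters only if the list could not be read.

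**3. What a bias would do, under assumptions only.** No document gives a rate or strength of selection. Suppose a share of one arm were replaced by infants whose 12-month fat mass differs by 1 SD (0.6 kg), with 100 analysed per arm (125 less 20%). SE = 0.6 × √(2/100) = 0.0849 kg. Type I error = 1 − Φ(1.96 − b/SE) + Φ(−1.96 − b/SE).

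| Share replaced (assumed) | Bias b | b as share of 0.24 kg | Two-sided type I error |
|---|---|---|---|
| 5% | 0.03 kg | 12.5% | 6.4% |
| 10% | 0.06 kg | 25% | 10.9% |
| 20% | 0.12 kg | 50% | 29.3% |

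This shows sensitivity. It is not an estimate for this trial.

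**4. Which baseline check fits the fault.** A Berger-Exner type check asks whether baseline features depend on the probability of the Nordic arm predicted from past allocations in the block. If the list was readable, selection follows the actual arm and not that prediction. In a simulation of 25 blocks of 10, with 10% of one arm shifted by 1 SD, the check rejected in 6.6% of 3,000 runs unadjusted and 5.4% adjusted for arm, close to the 5% expected with no selection. A clean result would reassure falsely.

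A direct comparison by arm looks in the right place, but it is also weak against a shift this small. With 125 per arm and a mean shift of 0.1 SD, z = 0.1/√(2/125) = 0.79, and power = 1 − Φ(1.17) + Φ(−2.75) ≈ 12%. The audit of the list must therefore carry most of the weight.

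**The case against.** The strongest reply has four parts.

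- *Available to is not the same as readable.* A list can be coded or covered, and a journal article may leave that to the full protocol. This stands in part. A reader might infer that allocation was in fact open to the nurses. The text does not prove it, and the sponsor may be able to document masking. What remains is that the article itself fixes who has the list and describes no safeguard, so this is a stated arrangement and not a detail merely left out.
- *The scope for selection is narrow.* Invitations go to all infants in the municipality, parents choose the time, entry is consecutive, the researchers check eligibility, and the study physician decides on biochemical exclusions. This also stands in part. Consecutive entry limits reordering along the list. It does not prevent a delay, a discouraging conversation or an exclusion once the next arm is known.
- *The size is invented.* A reader might take 10.9% as this trial's type I error. The documents do not support that: nothing in them gives the share replaced or the 1 SD difference. The figure has meaning only within the labelled range above.
- *The block size is a matter of preference.* Largely accepted. Ten is a fairly large block, sex-only stratification is no defect in a single-centre trial, and predictability from past allocations adds nothing if the list is readable.

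**Conclusion.** The concern holds in limited form. As described, allocation concealment is not assured: the list is available to the staff who enter participants and no coding or masking is mentioned. Selection could act through delay, discouragement or exclusion at baseline. That bias occurred is not shown, and its size in fat mass cannot be calculated from the documents.

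The conclusion rests on reading the article's sentence as a full account of how the list was held. Documented masking would reduce the point to the secondary one of a fixed block size (65% guessable, 17% certain, if past allocations were known). It merits action despite closed recruitment, because the remaining safeguards are cheap and the outcome has no baseline measurement.

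**What to change.** The design can no longer change, so act in the analysis plan and the report.

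1. **Report the arrangement.** Say who could see the list and whether it was coded or masked. Unless masking can be documented, state that allocation was not concealed from the enrolling staff.
2. **Audit the saved list.** For boys and girls separately, check that lines were used consecutively and that the dates of consent, eligibility confirmation and any exclusion are consistent with the allocation order. Report exclusions after allocation by arm, with reasons.
3. **Compare baseline features directly by arm:** weight, length, feeding mode and parental size, all of which the article plans to collect. Do not rely on a predicted-probability check, and do not present a balanced table as proof of no selection.
4. **Fix the primary model before unblinding.** Adjust the fat-mass comparison for sex (the stratification factor), baseline weight, baseline length and feeding mode. This replaces the wording in Power calculation and statistical analyses that leaves the choice of confounders open. Adjustment covers only differences carried by these variables.

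Cost: a few hours of data work and some wording, with the possible downside of an openly stated limitation. The sample size is unaffected.
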